## Abstract

**Background**: Early surgical intervention is associated with improved outcomes in hip fracture care, yet in patients using Direct Oral Anticoagulants (DOACs), surgery is frequently delayed due to concerns about increased intraoperative bleeding. Despite the increasing prevalence of hip fracture patients on DOACs, no consensus exists on optimal surgical timing. This has led to substantial practice variation between hospitals, with some operating within 24 h of last DOAC intake and others delaying surgery beyond 24 h. This study hypothesizes that early surgery within 24 h results in a non-inferior blood transfusion risk compared to delayed surgery 24 h or more after last DOAC intake in hip fracture patients on DOACs. This protocol describes the design and methodological rationale of a natural experiment. **Methods and analysis**: A multicenter cohort study designed as a natural experiment will be conducted across seven Dutch level 2 trauma centers, using predefined and standardized prospectively collected variables from electronic health records. Centers will adhere to distinct local surgical timing protocols, forming two cohorts: early surgery within 24 h and delayed surgery 24 h or more after last DOAC intake. Patients presenting with an isolated hip fracture who are using a DOAC and have taken their last dose within 24 h before admission will be included. The primary endpoint is postoperative blood transfusion. Secondary endpoints include additional bleeding-related outcomes, thrombotic and postoperative complications, and hospital length of stay. The primary analysis will be conducted on a per-protocol basis, with an intention-to-treat analysis performed as a supplementary assessment. Non-inferiority will be established if the upper bound of the one-sided 95% confidence interval for the risk difference does not exceed the predefined margin of 5%. **Ethics and dissemination**: Ethical approval was obtained from the Medical Ethics Committee United, Utrecht, The Netherlands. As this is a cohort study without altering clinical care, individual informed consent is not required. All data will be pseudonymized, and findings will be disseminated through peer-reviewed journals and scientific conferences. **Registration details**: Medical Ethics Committee United, Utrecht, The Netherlands, registration number W25.034.

## 1. Strengths and Limitations

This study addresses an urgent and clinically relevant knowledge gap regarding the optimal surgical timing for hip fracture patients on direct oral anticoagulants, with the potential to improve national and international guidelines.It utilizes a natural experiment design across seven Dutch trauma centers, leveraging existing practice variation to approximate randomization and enable real-world comparison of early surgery within 24 h versus delayed surgery 24 h or more after last direct oral anticoagulant intake, without interfering with routine clinical care, enhancing the generalizability of the findings.While the retrospective data extraction from electronic health records at predefined intervals is a limitation, all variables are prospectively predefined and standardized across participating hospitals, and regular data quality checks with structured feedback to centers are implemented to ensure consistency, completeness, and high data quality.Due to the limited number of covariates allowed in the regression model to prevent overfitting, there remains a risk of residual confounding; however, the most clinically relevant confounders will be accounted for in the analysis.A per-protocol primary analysis may be susceptible to confounding by indication; however, a pre-planned intention-to-treat analysis will assess the robustness of findings and mitigate this bias. In addition, time-dependent confounding cannot be fully excluded. Clinical or logistical factors arising during the preoperative waiting period, such as medical optimization, complications, or operating room availability, may influence both surgical timing and outcomes independent of direct oral anticoagulant status.

## 2. Introduction

Early surgical intervention is the standard of care for hip fractures, and there is robust evidence that shorter time to surgery improves patient outcomes, whereas delays are associated with higher mortality and worse outcomes, including prolonged immobility, extended hospital length of stay (HLOS), and greater patient discomfort [1,2,3,4,5,6,7,8]. However, in hip fracture patients on direct oral anticoagulants (DOACs), surgery is often postponed due to concerns about increased intraoperative bleeding risk while the anticoagulant is still active [9,10,11]. Although reversal agents for DOACs such as idarucizumab and andexanet alfa are now available, their high cost has limited their widespread adoption [12,13]. 

The clinical importance of this dilemma is particularly relevant given that hip fractures are among the most common causes of hospital admission in older patients and are associated with high mortality and a loss of independence [14]. Nationwide registry data indicate that nearly 20,000 hip fractures occur annually in The Netherlands [15]. Hip fracture patients frequently have multiple comorbidities and cognitive disorders, further increasing their vulnerability to poor outcomes [16,17,18]. Cardiovascular disease requiring long-term anticoagulation is particularly common, and DOACs have largely replaced vitamin K antagonists and heparins due to their predictable pharmacokinetics, fixed dosing, and limited monitoring requirements [19,20,21,22,23,24,25,26]. Currently, 12–16% of hip fracture patients require long-term anticoagulation with DOACs [19,20,21]. DOACs target different sites in the coagulation cascade, either as direct factor Xa inhibitors (apixaban, edoxaban, rivaroxaban) or as a direct factor IIa inhibitor (dabigatran) [27]. Their half-life is typically 10–14 h but may be prolonged up to 27 h in older patients due to reduced renal clearance and altered distribution, adding further uncertainty on surgical timing decisions (Appendix A; Table A1) [27,28]. This is particularly relevant for dabigatran, which is predominantly cleared renally [27,28].

Despite its clinical relevance, no consensus exists in the literature on the optimal surgical timing after DOAC discontinuation in hip fracture patients [12,27,29]. The uncertainty about this dilemma is reflected in clinical practice: 74% of surgeons consider current guidelines for hip fracture patients on DOACs inadequate, contributing to substantial clinical practice variation across hospitals [12,13,30,31]. Consequently, some hospitals postpone surgery for at least 48 h to mitigate bleeding risk, and some determine the timing of surgery based on renal function [12,13,30]. Retrospective studies suggest that early surgery may be safe; however, only one single-center study has directly compared the outcome of surgery performed within 24 h to after 24 h or more [27,32,33,34]. Nonetheless, expert consensus in several Dutch hospitals now permits immediate surgery for hip fracture patients on DOACs, as concerns also extend to preoperative blood loss from ongoing bleeding in unstabilized fractures [35,36,37].

This study will evaluate whether surgery within 24 h after last DOAC intake is as safe as surgery after 24 h or more in hip fracture patients on DOACs with respect to bleeding risk. Postoperative blood transfusion was chosen as the primary outcome because it represents a clinically relevant and objectively recorded outcome in routine practice. The hypothesis is that early surgery within 24 h results in a non-inferior postoperative blood transfusion risk compared to delayed surgery 24 h or more after last DOAC intake in hip fracture patients on DOACs. This protocol article outlines the design and methodological rationale of a natural experiment.

## 3. Clinical Relevance

The findings of this study will be particularly significant for the hip fracture population for several reasons. There is currently no consensus on the optimal timing of surgery for hip fracture patients on DOACs, leading to considerable clinical practice variation in discontinuation protocols across The Netherlands [12,13,27,30,31]. Clear, evidence-based recommendations are urgently needed to standardize care and improve outcomes in this vulnerable and growing patient population [31,38].

If early surgery is shown to be non-inferior with respect to bleeding and thrombotic complications, this would support a paradigm shift toward performing hip fracture surgery within 24 h of last DOAC intake. This could lead to reduced hospital length of stay, faster mobilization and rehabilitation, and lower the risk of complications related to immobilization such as pressure ulcers and nosocomial infections [39,40]. Moreover, the reduction in HLOS could lead to significant cost savings for healthcare systems, as well as improved capacity and resource utilization [40,41].

If early surgery is proven inferior to delayed surgery, this study will help to define the optimal timing of surgery after DOAC discontinuation, possibly based on renal function and drug clearance. This could enable widespread (inter)national implementation of standardized perioperative protocols, ultimately contributing to evidence based, safe, and more efficient hip fracture care.

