## 4. Objectives

### 4.1. Primary Objective

To determine whether early surgery within 24 h after last DOAC intake compared with delayed surgery after 24 h or more results in a non-inferior blood transfusion risk in hip fracture patients on DOACs, where non-inferiority is defined as the upper bound of the one-sided 95% confidence interval for the absolute risk difference remaining below a predefined margin of 5%.

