### 4.2. Secondary Objectives

-To investigate the effect on other bleeding-related outcomes in this population (i.e., preoperative blood transfusions, pre- and postoperative hemoglobin difference, the bleeding index, amount of packed red blood cells administered, reoperation due to postoperative bleeding or infection, sciatic neuropraxia due to postoperative bleeding or infection, postoperative anemia and postoperative hematoma).-To investigate the effect on thromboembolic outcomes in this population (such as acute myocardial infarction, stroke, pulmonary embolism, peripheral arterial thrombosis, and deep venous thrombosis).-To investigate the effect on postoperative complications in this population (i.e., wound fluid leakage, pressure ulcer, congestive heart failure, delirium, renal insufficiency, pneumonia, urinary tract infections, deep or superficial surgical wound infection, and in-hospital falls).-To investigate the effect on in-hospital and 30-day mortality in this population.-To investigate the effect on hospital length of stay and discharge destination in this population.

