### 5.7. Sample Size and Rationale for Non-Inferiority

The research question of this study is framed as a non-inferiority comparison, and the sample size has therefore been calculated to test non-inferiority. This study used the most recent institutional data, as these best reflect the clinical context and patient population of this study. These institutional data showed a transfusion rate of approximately 15% in the delayed surgery group and 10% in the early surgery group, which is considered appropriate for powering a non-inferiority analysis in this natural experiment. In consultation with clinical experts, a non-inferiority margin (ΔNI) of 5% is deemed clinically acceptable to conclude that early surgery does not result in a clinically relevant increase in transfusion requirement. Non-inferiority will be demonstrated if the upper bound of the one-sided 95% confidence interval for the absolute risk difference between groups remains below 5%. Based on these assumptions, an expected event rate of 15% in the control group and 10% in the intervention group, with a one-sided alpha of 0.05 (Zα = 1.645) and a power of 90% (Zβ = 1.282), the required total sample size is 374 patients, with 187 per group.

As the sample size is based on the per-protocol population, patient inclusion will continue until 187 patients per treatment group have been included who adhered to the protocol of their respective school of treatment (Figure 2). Inclusion in a given school will stop once the required number of per-protocol patients (*n* = 187) is reached in that group. The other school will continue including patients until it also reaches the target of 187 per-protocol patients. As a result, the intention-to-treat population is expected to exceed 374 patients. Since the primary outcome is assessed during hospitalization, no loss to follow-up is anticipated. This approach provides sufficient power to robustly assess non-inferiority within the specified parameters.

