#### 5.8.2. Secondary Outcomes

Secondary outcomes will be analyzed according to the type and distribution of each variable. Continuous variables (i.e., Hb decrease, bleeding index, surgery duration, time to DOAC restart, hospital length of stay) will first be assessed for normality using graphical methods (e.g., histograms). Normally distributed outcomes will be analyzed using parametric tests, specifically independent-sample t-tests. If the distribution is non-normal, non-parametric methods, such as the Mann–Whitney U test, will be applied. Ordinal or categorical variables with more than two categories, such as the number of packed red cell units transfused, will be analyzed using the Chi-square test. Binary outcomes, including thromboembolic events, postoperative complications, and a Hb decrease of more than 2 mmol/L, will be analyzed using Chi-square tests, or Fisher’s exact test in cases where expected cell counts are less than five.

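### Section 3 makes a change of practice depend on non-inferiority for thrombotic complications, but only transfusion has a margin and decision rule, and the tests set for thromboembolic events cannot show it

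*Protocol article*

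**What the plan says.** Section 3 (Clinical Relevance) sets out what a favourable result would mean. A move towards operating within 24 h of the last dose would be supported, provided that early surgery proves "non-inferior with respect to bleeding and thrombotic complications".

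The operative sections are narrower:

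- Section 2 (Introduction): "The hypothesis is that early surgery within 24 h results in a non-inferior postoperative blood transfusion risk compared to delayed surgery".
- Section 4.1 (Primary Objective): the aim is to determine whether early surgery "results in a non-inferior blood transfusion risk in hip fracture patients on DOACs". The margin is 5% on the absolute risk difference, judged by a one-sided 95% upper bound.
- Sections 5.7 and 5.8.1: the sample size (187 per group, 374 in total) and the decision rule are both for transfusion.
- Section 4.2 (Secondary Objectives): "To investigate the effect on thromboembolic outcomes in this population", with no non-inferiority wording and no margin.
- Section 5.8.2 (Secondary Outcomes): "Binary outcomes, including thromboembolic events, postoperative complications, and a Hb decrease of more than 2 mmol/L, will be analyzed using Chi-square tests". The fallback when expected counts fall below five is Fisher's exact test.

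**The concern.** To say that a treatment has been shown non-inferior is a technical claim. It needs a margin fixed in advance and an interval compared with that margin. Chi-square and Fisher tests ask whether two rates differ. A significant result in favour of delay would count against early surgery. A non-significant result says only that a difference was not detected. Neither outcome excludes an increase of a given size.

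Section 3 therefore attaches the study's practice message to a statement about thrombotic safety for which the article provides no means of proof. If thrombotic events are rare, 187 patients per group will often miss even a large relative increase, so the absence of a significant difference would carry little weight.

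**Working it through.** **1. The plan's own figure, and what it covers.** Inputs from section 5.7: 15% transfused in the delayed group, 10% in the early group, margin 5%, one-sided alpha 0.05 (1.645), power 90% (1.282).

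n per group = [0.15×0.85 + 0.10×0.90] × (1.645 + 1.282)² / (0.05 + 0.05)² = 0.2175 × 8.567 / 0.01 ≈ 186.3, so 187 per group and 374 in total. The stated figure reproduces. Every input is a transfusion quantity, so the 90% power says nothing about thrombotic events.

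**2. What 187 per group can say about thrombotic events.** The article gives no thrombotic rate. The delayed-group rates below are assumptions, shown as a range.

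- *Chance of detecting a doubling* (p against 2p, two-sided 5% chi-square): power = Φ[(p − 1.96×SE₀)/SE₁]. Here SE₀ = √(2×p̄(1−p̄)/187) with p̄ = 1.5p, and SE₁ = √((p(1−p) + 2p(1−2p))/187). At 3% against 6%: SE₀ = 0.02144, SE₁ = 0.02138, (0.03 − 0.04202)/0.02138 = −0.562, and Φ = 0.287.
- *Precision if the rates are equal*: half-width of the two-sided 95% interval = 1.96 × √(2p(1−p)/187). At 3%: 1.96 × √(0.0582/187) = 0.0346.

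| Assumed delayed-group rate | Chi-square power for a doubling | Fisher power for a doubling | 95% CI half-width, equal rates |
|---|---|---|---|
| 2% | 20% | 12% | 2.8 points |
| 3% | 29% | 21% | 3.5 points |
| 5% | 45% | 38% | 4.4 points |

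A simulation of 20,000 draws that switches to Fisher when an expected count is below five gives 18%, 28% and 45%, in line with the chi-square column. On those simulated figures a true doubling would come out non-significant in about 82%, 72% and 55% of studies.

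**3. What showing non-inferiority would take.** The article sets no thrombotic margin. Purely as an illustration, take a margin equal to the delayed-group rate, which amounts to ruling out a doubling. With equal true rates, one-sided 5% and 90% power, n per group = 2p(1−p) × 8.567 / p². This gives 840 at 2%, 554 at 3% and 326 at 5%, all above 187.

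**The case against.** Four arguments can be made on the other side.

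**Section 3 is rationale, not a decision rule.** Its sentence is conditional and describes possible implications, while the hypothesis, primary objective, sample size and analysis all confine non-inferiority to transfusion. This stands. A reader might infer that the study plans to declare thrombotic non-inferiority from p > 0.05. The documents do not support that: no section says a non-significant test will be read in that way, and section 4.2 speaks only of investigating the effect. What remains is a mismatch. Section 3 names a condition that the analysis described cannot satisfy.

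**Bleeding is arguably covered.** Section 2 frames safety in terms of bleeding risk and chooses transfusion as the primary outcome, and section 5.5.1 treats transfusion as a marker of perioperative blood loss. This also stands. The gap is firm for thrombotic complications only.

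**Intervals for secondary outcomes are commonly left to the full plan.** True, and the lack of intervals is not in itself the fault. But the article states both the claim and the tests, and the two do not fit. An analysis plan that added intervals would still not correct the wording of section 3.

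**The size rests on assumed rates and on the per-protocol minimum.** Also true. Section 5.7 expects the intention-to-treat set to exceed 374, which would help precision somewhat. On the study's own one-sided 95% convention, the upper bound at equal rates is 1.645 × √(2p(1−p)/187) = 2.4, 2.9 and 3.7 points, somewhat tighter than the two-sided half-widths. Power to detect a doubling is still below one half throughout the range.

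**Conclusion.** The point holds as an inconsistency between the stated implication and the stated analysis. Section 3 asks for non-inferiority on thrombotic complications, while sections 4.1, 5.7 and 5.8.1 provide the means to show it for transfusion alone and section 5.8.2 gives thromboembolic events difference tests.

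At assumed rates of 2% to 5%, the planned chi-square test has about 20% to 45% power to detect a doubling. A non-significant finding could not support the safety half of the practice message. These percentages depend on the assumed rates and on 187 per group. The logical mismatch depends on neither.

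The primary comparison, its margin and its sample size are not affected.

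**What to change.** - **Section 3:** limit the non-inferiority wording to postoperative transfusion, and say that thrombotic outcomes will be described alongside it.
- **Section 5.8.2:** report thromboembolic events (any event, and each listed type) as unadjusted risk differences with 95% confidence intervals, labelled exploratory. State that a non-significant test is not evidence of non-inferiority.

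Unadjusted differences are the practical choice. Section 5.8.1 allows five variables for about 56 events. At an assumed 3% there would be about 0.03 × 374 ≈ 11 thrombotic events in all, enough for roughly one variable on the same rule, and each separate type would be rarer still.

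The cost is a few sentences and the reporting of intervals, with no extra patients or data. The price is a narrower claim: a favourable primary result would support early surgery on transfusion, with thrombotic safety described but not established.

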## 4. Objectives

### 4.1. Primary Objective

To determine whether early surgery within 24 h after last DOAC intake compared with delayed surgery after 24 h or more results in a non-inferior blood transfusion risk in hip fracture patients on DOACs, where non-inferiority is defined as the upper bound of the one-sided 95% confidence interval for the absolute risk difference remaining below a predefined margin of 5%.

### 4.2. Secondary Objectives

-To investigate the effect on other bleeding-related outcomes in this population (i.e., preoperative blood transfusions, pre- and postoperative hemoglobin difference, the bleeding index, amount of packed red blood cells administered, reoperation due to postoperative bleeding or infection, sciatic neuropraxia due to postoperative bleeding or infection, postoperative anemia and postoperative hematoma).-To investigate the effect on thromboembolic outcomes in this population (such as acute myocardial infarction, stroke, pulmonary embolism, peripheral arterial thrombosis, and deep venous thrombosis).-To investigate the effect on postoperative complications in this population (i.e., wound fluid leakage, pressure ulcer, congestive heart failure, delirium, renal insufficiency, pneumonia, urinary tract infections, deep or superficial surgical wound infection, and in-hospital falls).-To investigate the effect on in-hospital and 30-day mortality in this population.-To investigate the effect on hospital length of stay and discharge destination in this population.

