#### 5.5.2. Secondary Outcomes

Secondary outcomes include a broad range of bleeding-related outcomes, thrombotic complications, and postoperative complications, and healthcare resource utilization. Bleeding-related outcomes include preoperative blood transfusion, the number of PRBCs administered (1, 2, 3, or ≥4 units), lowest postoperative Hb and Ht levels within 24 h postoperatively, Hb decrease (ΔHb) (defined as the difference between preoperative Hb (measured at the ED) and the lowest postoperative Hb within 24 h), the bleeding index (defined as ΔHb plus the number of PRBC transfused between the ΔHb period), the number of patients experiencing a Hb decrease of more than 2 mmol/L. Estimated intraoperative blood loss will not be recorded, as it is considered too subjective, prone to outcome reporting bias, and highly susceptible to inter-rater variability. Clinical complications such as reoperation due to postoperative bleeding or infection, sciatic neuropraxia due to postoperative bleeding or infection, postoperative hematoma, and postoperative anemia will also be recorded. Lastly, administration of tranexamic acid, fibrinogen, or platelet concentrates will also be assessed.

Thrombotic complications recorded in this study comprise myocardial infarction (confirmed by electrocardiogram), stroke (confirmed by CT), pulmonary embolism (confirmed by CT-Angiography), deep vein thrombosis (confirmed by ultrasound), and peripheral arterial thrombosis (confirmed by CT-Angiography).

Other postoperative complications as determined by the Dutch Hip Fracture Audit guidelines will be assessed and include pressure ulcers, delirium, deep or superficial surgical wound infections, wound fluid leakage, days of wound fluid leakage, congestive heart failure, and in-hospital falls (all diagnosed by the attending physician or geriatrician) [54]. Additional complications include pneumonia (confirmed by chest radiograph or positive sputum culture), urinary tract infections (confirmed by a positive urine culture), renal insufficiency (defined as a >24 mL/min/1.73 m^2^ decrease in eGFR compared to admission), in-hospital mortality (recorded in hospital records), and 30-day mortality (determined through municipality records) [54].

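### Delirium, pressure ulcer, heart failure, pneumonia and urinary tract infection carry a postoperative label, so a count that starts at surgery can omit harm from the preoperative wait, and more of it in School B

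*Protocol article*

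**What the plan says.** The postoperative label appears in the objective, the outcome definition and the analysis.

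- **Objective (Section 4.2):** "To investigate the effect on postoperative complications in this population (i.e., wound fluid leakage, pressure ulcer, congestive heart failure, delirium, renal insufficiency, pneumonia, urinary tract" infections, wound infection and in-hospital falls.
- **Outcome (Section 5.5.2):** "Other postoperative complications as determined by the Dutch Hip Fracture Audit guidelines will be assessed and include pressure ulcers, delirium", then wound items, congestive heart failure and falls. Pneumonia and urinary tract infection follow in a separate sentence that gives no onset window: "Additional complications include pneumonia (confirmed by chest radiograph or positive sputum culture".
- **Analysis (Section 5.8.2):** postoperative complications are compared between groups by Chi-square or Fisher's exact test.

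Other outcomes are treated differently in Section 5.5.2. Preoperative transfusion is an outcome of its own ("Bleeding-related outcomes include preoperative blood transfusion"). Thrombotic events carry no postoperative restriction ("Thrombotic complications recorded in this study comprise myocardial infarction (confirmed by electrocardiogram"). Renal insufficiency is a "decrease in eGFR compared to admission". Length of stay runs from ED presentation.

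Two other places bear on the point. Section 3 expects that early surgery could "lower the risk of complications related to immobilization such as pressure ulcers and nosocomial infections". Section 1 mentions "Clinical or logistical factors arising during the preoperative waiting period, such as medical optimization, complications, or operating room availability" as influences on both timing and outcome, that is, as a source of confounding and not as an outcome.

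**The concern.** The two schools differ in how long a patient waits before surgery. Harm that arises during that wait is a consequence of the policy and belongs in the comparison of policies. If the complication clock starts at surgery, it starts later after arrival in School B than in School A. An event at a given hour after arrival can then count in School A, where the patient has been operated on, and not in School B, where the patient is still waiting.

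At stake are the secondary comparisons for pressure ulcer, delirium, heart failure, pneumonia and urinary tract infection. Pressure ulcers and nosocomial infections are the immobilization harms that Section 3 expects early surgery to reduce. Losing events from the longer wait would weaken the test of that benefit and could hide it.

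**Working it through.** **1. The plan's own figure.** The article gives no complication rate and no sizing for complications. Its only sizing figure is for the primary outcome (Section 5.7), and it reproduces: [0.15 × 0.85 + 0.10 × 0.90] × (1.645 + 1.282)² / (0.05 + 0.05)² = 186.3, so 187 per group and 374 in total. Nothing below touches it.

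**2. Does the label carry meaning?** Where the authors want the preoperative period they say so, as with preoperative transfusion and length of stay from ED presentation. For pressure ulcer, delirium and heart failure, the label stands in both objective and outcome. For pneumonia and urinary tract infection it stands in the objective only. No section writes out a counting start for any of the five.

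**3. Do waits from ED presentation differ?** The 24 h threshold runs from last DOAC intake (Section 5.2.2), and intake may be up to 24 h before ED presentation (Section 5.3). Let t be the hours from last dose to ED presentation. Among protocol-adherent patients:

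- School A: wait from ED is within 24 − t hours.
- School B: wait from ED is at least 24 − t hours.

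For equal t, the School B wait is therefore the longer one. The size of the difference is not fixed and can be small. Across different t the order can reverse: with t = 14, School B may operate from 24 − 14 = 10 h after arrival, while with t = 2, School A may operate up to 24 − 2 = 22 h after arrival. So the direction on average follows if t is distributed similarly in the two schools; the size needs data.

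**4. Illustration with no true difference (all inputs assumed).** Let R be the in-hospital risk in each school, with constant hazard over 7 days (168 h): h = −ln(1 − R)/168. A postoperative-only count misses 1 − exp(−h × wait). Take a wait of 12 h in School A and 30 or 48 h in School B. For R = 20%, h = 0.00133 per hour; School A misses 1.6 points and School B misses 3.9 or 6.2.

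| True risk, both schools | False excess for early surgery, 12 vs 30 h | 12 vs 48 h |
|---|---|---|
| 10% | 1.1 points | 2.2 points |
| 20% | 2.3 points | 4.6 points |
| 30% | 3.7 points | 7.2 points |

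**5. Same question with assumed onset shares.** Take 20% risk in both schools. If 10–30% of School B events start before surgery, the count is 20% × 0.90 = 18% down to 20% × 0.70 = 14%. If 0–10% of School A events do, it is 20% down to 18%. The false excess is 18 − 18 = 0 up to 20 − 14 = 6 points.

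**6. Illustration with a true benefit.** Assume 25% in School B and 20% in School A, a true difference of −5 points. The observed difference is 20% × (1 − share in A) − 25% × (1 − share in B):

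- shares 10% and 20%: 18 − 20 = −2 points
- shares 20% and 40%: 16 − 15 = +1 point
- shares 10% and 40%: 18 − 15 = +3 points

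**7. Persistence.** If a fraction q of events that begin before surgery is still recorded as postoperative, equally in both schools, the bias in step 4 shrinks by the factor 1 − q. With q = 0.5, the 2.3 to 4.6 points become about 1.2 to 2.3.

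**The case against.** The strongest reply is that a strict postoperative window is inferred from a label. The label is used loosely: the list in Section 4.2 also holds renal insufficiency, which is measured against admission, and in-hospital falls. Section 5.5.2 refers to audit definitions that are not shown, and Section 5.6 to a standardized variable set that is not shown; either may fix an onset window. A patient who is delirious before and after surgery may well be recorded. The difference in waits from arrival is unknown, and every illustrative figure is assumed, with one range reaching zero.

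Most of this stands, and it limits the claim. It does not remove the point. The article states the word postoperative in objective, outcome and analysis, and names preoperative events separately where it wants them. Followed as written, the clock starts at surgery. If the unseen definitions start it at admission, the published wording needs correcting instead.

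A reader might also infer that all preoperative harm is left out. It is not: preoperative transfusion, thrombotic events, mortality, length of stay and renal insufficiency are not confined to the period after surgery.

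**Conclusion.** The point holds for five named secondary outcomes: pressure ulcer, delirium, congestive heart failure, pneumonia and urinary tract infection. As labelled, their count can omit more harm in School B than in School A, which would tend to bias those comparisons against early surgery. This rests on two assumptions: that the label is applied as a counting window, and that the interval from last dose to arrival is similar between schools.

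The size cannot be derived from the documents. At an assumed 20% risk, the illustrations give 2.3 to 4.6 points under one model and 0 to 6 under another. Both treat every event that begins before surgery as lost, and shrink if persisting events are recorded.

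Two stronger readings are not supported. A reader might infer that the bias is established; the documents give no counting rule, rates or waits to show that. A reader might infer that the study cannot test its stated benefit at all. Length of stay, which Section 3 also names, is measured from ED presentation and remains testable, and the hypothesis itself concerns transfusion. The primary non-inferiority comparison and the 374-patient sample size are unaffected.

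**What to change.** For the five named complications, define the between-school outcome as new onset from ED presentation to discharge, in both schools. Record whether onset was before or after surgery, and report the postoperative-only count as a split. Keep wound-specific items (wound leakage, wound infection) postoperative, since they cannot precede surgery. State the window in Section 5.5.2 and align the wording in Sections 4.2 and 5.8.2.

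The cost is an onset date per event from the health records that are already extracted at several time points (Section 5.6), so slightly more extraction work and no change in care. The main count becomes less directly comparable with audit figures, if those count only postoperative events; the split supplies the postoperative-only figure.
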